**Methods:**

This study involves a parallel-group, assessor-blinded RCT that examines the effect of a 4-month home-based exercise training intervention on depression severity in a sample of persons with MS who have MDD based on the MINI International Neuropsychiatric Interview. The primary outcomes of depression severity are the Patient Health Questionnaire-9 and Hamilton Depression Rating Scale. Participants (*N* = 146) will be recruited from within 200 miles of the University of Illinois at Chicago and randomized (1:1) into either a home-based exercise training condition or control condition with concealed allocation. The exercise training and social-contact, attention control (i.e., stretching) conditions will be delivered remotely over a 4-month period and supported through eight, 1:1 Zoom-based behavioral coaching sessions guided by social-cognitive theory and conducted by persons who are uninvolved in screening, recruitment, random assignment, and outcome assessment. We will collect outcome data at 0, 4 and 8 months using treatment-blinded assessors, and data analyses will involve intent-to-treat principles.

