#### Power analysis and sample size

The power analysis was conducted in G*Power, Version 3.1 using F test for Test family and ANOVA: Repeated measures, within-between interaction for Statistical test. We estimated the sample necessary for detecting a Condition (2 levels of between-subjects factor: Intervention vs. Control) × Time (2 levels of within-subjects factor: 0 and 4 months) interaction on the primary outcomes of depression severity (i.e., 9-item Patient Health Questionnaire (PHQ-9; [36]) and Hamilton Depression Rating Scale (HDRS-17; [37]). We did not include 3 time-points as this assumes linear change across all 3 time points in G*Power 3.1, and we expected change between 0 and 4 months for the intervention condition, followed by stability between 4 and 8 months. The effect size (Cohen’s *f* = 0.18) was from our previous meta-analyses [15] regarding the effect of exercise training on depressive symptoms in persons with MS. The power analysis included assumptions of reliability for the within-subjects factor of ICC = 0.50, two-tailed *α* = 0.025, and *β* = 0.05 (i.e., 95% power); the *α* = 0.025 was selected based on two primary outcomes. The power analysis indicated the minimal total sample size for testing the Time × Condition interaction of 122 participants (61 per group), and we anticipate a dropout rate of ~ 20% resulting in a projected recruitment of 146 participants.

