### Data analyses

#### Overview

The data analyses will be overseen by a biostatistician and follow intent-to-treat (ITT) principles (i.e., include all persons regardless of dropout). We will perform exploratory data analyses only among those who complete immediate and long-term follow-up testing (i.e., completer’s or per protocol analysis). We will check the data for errors and outliers, and lock the data set before analyses. The analytic plan will account for potential confounders of the intervention effect on the outcomes. The confounders may include MS duration, BMI, age, sex, disease-modifying therapy, and relapse rate. We will include any of those variables and others that differ between conditions as covariates in the following analyses.

#### Data analysis – aim 1

The first analysis tests the hypothesis that those who are randomly assigned into the intervention condition (i.e., exercise training) will demonstrate (a) reductions from baseline in depression severity that (b) are sustained over 4-months of follow-up compared with those in the control condition (i.e., stretching). The hypothesis will be tested using a linear mixed model in JMP Pro 16.0. The linear mixed model will include condition and time as fixed effects, and subject nested within condition as a random effect using unbounded variance components and the REML method (https://www.jmp.com/content/dam/jmp/documents/en/academic/learning-library/08-repeated-measures-analysis-(mixed-model).pdf). The hypothesized interaction term will be decomposed with follow-up tests, and differences in comparison of mean scores will be expressed as Cohen’s d with standard guidelines for interpretation. The final models for PHQ-9 and HDRS-17 scores will be adjusted for covariates. The overall Type I error will be controlled based on an adjustment of alpha (two-tailed *α* = 0.025) given the two primary outcomes in Aim 1.

#### Data analysis – aim 2

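### With only a random subject effect, the Aim 1 model assumes compound symmetry at 0, 4 and 8 months, so the immediate and sustained contrasts can carry standard errors that are too small or too large

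*Protocol article*

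**What the plan says.** Outcomes are measured three times: "We will collect outcome data at 0, 4 and 8 months using treatment-blinded assessors" (Abstract, Methods).

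Under Data analysis – aim 1, "The linear mixed model will include condition and time as fixed effects", with "subject nested within condition as a random effect using unbounded variance components and the REML method". No residual covariance structure is named. The same section says "The hypothesized interaction term will be decomposed with follow-up tests". The hypothesis has two parts, a reduction from baseline and its maintenance over the next four months, each compared with control. Each primary outcome is tested at two-tailed alpha 0.025. The sections for aims 2 and 3 reuse the same model.

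The section Power analysis and sample size covers only 0 and 4 months, with "assumptions of reliability for the within-subjects factor of ICC = 0.50". It explains the choice of two visits by saying "we expected change between 0 and 4 months for the intervention condition, followed by stability between 4 and 8 months".

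**The concern.** Each participant belongs to one condition, so subject nested within condition is a random intercept. With independent residuals it implies the same variance at every visit and the same correlation between every pair of visits. Allowing unbounded variance components lets the subject variance be estimated as negative, but it does not relax this restriction.

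The immediate claim is the between-arm difference in 0-4 month change. The sustained claim rests on 0-8 month change, and possibly on 4-8 month change. Under compound symmetry all three contrasts get the same standard error. If the true variances of the three differences are unequal, at least one contrast is tested above its nominal level with an interval that is too narrow, and at least one is tested below it. Nothing in the article supports equality across three visits.

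**Working it through.** **The plan's own figure.** For a two-group, two-visit interaction, lambda = f² × N × 2/(1 − ICC) = 0.18² × N × 2/0.5 = 0.1296 N, with 1 and N − 2 degrees of freedom. At alpha 0.025, N = 120 gives power 0.952 and N = 122 gives 0.955. The stated 122 is reproduced within two participants. With two visits there is only one within-subject difference, so compound symmetry does no harm there. The problem starts with the third visit.

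**Inputs.** Alpha 0.025 two-sided is from the article. After 20% dropout, 146 × 0.8 = 116.8, or about 58 per arm. The SDs and the correlations involving 8 months are not given, so the values below are assumptions.

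**Formulas.** For visits i and j, the variance of the within-subject difference is v_ij = s_i² + s_j² − 2 r_ij s_i s_j. With complete, balanced data the random-intercept model replaces each v_ij by the mean v̄ = (v04 + v08 + v48)/3. Hence model SE / true SE = √(v̄ / v_ij), and type I error ≈ 2[1 − Φ(2.241 × ratio)].

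**One case in full.** With equal SDs of 1 and correlations 0.5 (0-4), 0.25 (0-8) and 0.5 (4-8):
- v04 = 2 − 1.0 = 1.0; v08 = 2 − 0.5 = 1.5; v48 = 1.0; v̄ = 3.5/3 = 1.167.
- 0-4 months: ratio √(1.167/1.0) = 1.08, size about 0.016.
- 0-8 months: ratio √(1.167/1.5) = 0.88, size about 0.048.

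**Range.** Sizes are simulated: 58 per arm, complete data, 40,000 runs, no gating on the interaction test. Correlations are in the order 0-4 / 0-8 / 4-8. Each cell gives the SE ratio, then the size.

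| Assumed pattern | 0-4 months | 0-8 months | 4-8 months |
|---|---|---|---|
| Equal SD, 0.5/0.5/0.5 | 1.00; 0.025 | 1.00; 0.025 | 1.00; 0.023 |
| Equal SD, 0.5/0.4/0.7 | 0.97; 0.030 | 0.88; 0.049 | 1.25; 0.006 |
| Equal SD, 0.5/0.4/0.8 | 0.93; 0.036 | 0.85; 0.056 | 1.47; 0.001 |
| Equal SD, 0.5/0.25/0.5 | 1.08; 0.016 | 0.88; 0.048 | 1.08; 0.016 |
| Baseline SD 0.75 of follow-up, 0.5/0.5/0.8 | 0.91; 0.042 | 0.91; 0.040 | 1.30; 0.004 |
| Baseline SD 0.75 of follow-up, 0.5/0.5/0.5 | 1.04; 0.019 | 1.04; 0.021 | 0.94; 0.037 |
| Follow-up SD 1.25 × baseline, 0.5/0.5/0.5 | 1.03; 0.021 | 1.03; 0.022 | 0.95; 0.035 |
| Follow-up SD 0.8 × baseline, 0.5/0.5/0.5 | 0.96; 0.031 | 0.96; 0.032 | 1.10; 0.015 |

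With an unstructured covariance, each contrast uses its own variance and the size stays at 0.024 to 0.026 in every row.

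**The interaction test.** The 2-df test under the random intercept has size 0.026 to 0.036 in the rows that depart from compound symmetry. It is much less affected than the single contrasts.

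**The case against.** **Direction.** A reader might infer that both baseline contrasts are bound to be anti-conservative. The article does not support this. With decaying correlation the 0-4 month standard error is 8% too large. With equal correlations and larger follow-up SDs, both baseline contrasts are 3 to 4% too large.

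**Screening on depression.** One might argue that narrowed baseline spread makes the standard errors too small. Taken alone it works the other way: a baseline SD of 0.75 with all correlations 0.5 gives a ratio of 1.04. The inflation in the 0.5/0.5/0.8 row comes from the high 4-8 month correlation.

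**Expected pattern.** One might read the expected change and then stability as contradicting the model. That statement concerns means. Fixed effects for condition, categorical time and their interaction can represent a plateau under any covariance structure, and a plateau in means does not imply a higher 4-8 month correlation.

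**Gating.** The wording on decomposing the interaction suggests that it is tested first. If the contrasts are read only after a significant interaction, the global-null error in the three rows with a 4-8 month correlation of 0.7 or 0.8 falls to 0.017-0.024 at 4 months and 0.022-0.031 at 8 months. This stands, but only for the global null. If there is a real effect at 4 months and none at 8, a significant interaction is likely and the gate gives the 0-8 contrast little protection. Interval widths are never protected.

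**Condensed source.** The article may leave the residual structure to an analysis plan that is not at hand. This weakens the point but does not remove it, because the article does commit to a specific random-effects model.

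**Conclusion.** The point holds in limited form. The stated model imposes compound symmetry on three visits without justification, and the contrasts that answer the primary aim inherit one pooled variance.

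Under the assumed patterns, the nominal 0.025 becomes about 0.02 to 0.055 for 0-8 months and about 0.015 to 0.04 for 0-4 months. The 0-8 contrast is inflated in each pattern examined where its correlation is clearly the lowest. The 4-8 month contrast is conservative in most patterns, so loss of effect after coaching ends would be harder to detect. Where both occur, they favour a conclusion that the effect is sustained.

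These figures rest on assumed SDs and correlations, complete data, equal covariance in both arms and contrasts not gated on the interaction. They do not show that the trial will overstate its evidence. Nor do they show any inconsistency between the model and the expected course of the means. The interaction test itself is only modestly affected.

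**What to change.** Replace the random subject intercept with an unstructured 3 x 3 within-subject covariance, fitted by REML with Kenward-Roger degrees of freedom. Take the 0-4, 0-8 and 4-8 month between-arm contrasts from that model. Name in advance the fallback structure to use if it does not converge. Apply the same change to aims 2 and 3, which reuse the model. Nothing here requires a different primary hypothesis or primary test.

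The cost is six covariance parameters instead of two, four more, with about 146 participants, and slightly fewer error degrees of freedom per contrast. No new data or participants are needed. The article reports 18 people enrolled at its status date and a data lock before analysis, so the change can be fixed ahead of the results.

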### Current trial status

As of February 13, 2024 and reported in our quarterly report for the funder, we have enrolled 18 persons into the trial, and these persons have been equally randomized into the intervention and control conditions (9 per condition). There were 6 other persons scheduled for baseline testing and ready for randomization.

## Discussion

We are proposing a Phase-II RCT of exercise training for treating depression severity in persons with MS who have MDD. If successful based on statistically significant and clinically meaningful improvements in depression symptom outcomes (e.g., ½ SD improvement for exercise compared with control) [64] as well as retention exceeding 20% (primary decision rules), we will proceed with the design of a Phase-III clinical trial of exercise training compared with CBT alone and combined with exercise training for treating depression severity in persons with MS who have MDD. We propose the addition of CBT as it has been considered a “possibly efficacious” treatment for depression in MS [7, 8] and can be delivered remotely [9]. This is a logical next step, as the data gathered herein would power such a clinical trial and provide necessary experiences for a presumed larger trial. We further have experience in the conduct of Phase-III trials of exercise and physical activity in MS [21, 65], and our ongoing PCORI trial provides a benchmark for conducting a Phase-III clinical trial of exercise training compared with CBT for managing depression severity in persons with MS who have MDD. Such a Phase-III clinical trial would provide definitive evidence for transition into clinical care and practice of persons with MS who have MDD, perhaps serve as a benchmark for studying exercise training as a treatment of other outcomes in persons with MS – this is a major stumbling block in all MS research involving exercise training [66], including depressive symptoms in MDD [10].

We may experience problems with the participants adhering with the intervention and control conditions based on the lack of interest/pleasure in activities, sadness, tiredness/fatigue, or physical problems (e.g., pain) as part of MDD. We are minimizing this by using SCT-based content and strategies and 1:1 remote behavioral coaching for maximizing adherence with both conditions. We further are managing this by enrolling a smaller number of persons (n ~ 12) over 12, partially overlapping recruitment waves (i.e., 12 waves of ~ 12 participants per wave), and thereby having the behavior coaches devote a greater amount of time with the participants during the one-on-one chat sessions. This should permit greater penetration of the study materials and a larger change in behavior for both conditions. The power analysis was based on meta-analyses for the effect of exercise interventions on depressive symptoms in samples that were not prescreened for MDD, and the preliminary data might not represent the treatment effect for those with MDD. Of note, our secondary analysis of previously published data suggested that effect of a physical activity intervention on depressive symptoms was stronger in those with elevated scores [67], and this would suggest that our power analysis and sample size should be appropriate for detecting an intervention effect on depression in those with MDD. There may be some attrition during the 4-month follow-up period wherein there is no planned coaching/contact, but this has been minimal in our previous [68] and ongoing [21] trials using the sample general approach; this is expected as the conditions are designed around teaching people skills, techniques, and strategies for sustainable behavior change.

If successful, the proposed study will provide the first and only Class I evidence for a home-based exercise training program as a treatment of depression in persons with MS who have MDD. This is critical as exercise training would likely have secondary effects on symptoms, cognition, and HRQOL, and provide a powerful, behavioral approach for managing the many negative outcomes of MDD in MS. The program in the proposed research is accessible and scalable for broad-scale treatment of depression in MS, and provides the potential for integration in the clinical management of this disease.

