#### Attrition

We have experienced low attrition (10%) in our previous RCTs of the exercise training protocol in this proposal [19], and we note recent data from a meta-analysis suggesting an attrition rate of ~ 10% across 40 RCTs of exercise training in MS [33]. We believe attrition could be higher in this RCT based on depressive symptomology in MDD resulting in poor motivation and adherence for exercise engagement. We conservatively planned for a higher attrition rate of 20% for the proposed RCT, and recognize that retention might be a challenge, although we are including SCT-based content and 1:1 zoom-based behavioral coaching for maximizing retention and adherence [34] as is appropriate for persons with MS who have elevated depressive symptoms [35].

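### The Phase III go rule asks for retention above 20%, which is the planned attrition figure used as a retention threshold; it passes with almost 80% of participants lost

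*Protocol article*

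**What the plan says.** The Discussion sets out when the team will move on: "we will proceed with the design of a Phase-III clinical trial" if two conditions are met together. The first is "statistically significant and clinically meaningful improvements in depression symptom outcomes", with a half-SD advantage over control given as an example. The second is "as well as retention exceeding 20% (primary decision rules").

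The figure of 20% appears in two other places, both times as a loss rate. The Attrition section states: "We conservatively planned for a higher attrition rate of 20% for the proposed RCT". It calls this conservative against the team's own record: "We have experienced low attrition (10%) in our previous RCTs". The section on power and sample size starts from a minimum for the Time × Condition "interaction of 122 participants (61 per group") and allows for a dropout rate of about 20%, "resulting in a projected recruitment of 146 participants".

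The article gives no reason for a 20% retention floor and no other definition of retention.

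**The concern.** A plan built on 20% attrition expects about 80% retention. A rule that asks only for retention above 20% tolerates four times the planned loss, and it would fail only in a trial that had largely collapsed. The natural explanation is that the attrition figure was carried into the sentence and attached to the wrong word.

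The sentence matters because it is the only statement of the go rule in the article and is labelled primary. A retention condition beside an efficacy condition is there to stop progression when dropout has made the efficacy result unreliable. The Attrition section itself expects loss to be linked to depressive symptoms and poor motivation, so heavy loss here could be informative and could bias the estimate. A significant result among the few who remain is the case the condition should catch, and as written it would not.

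**Working it through.** **Inputs.** Recruitment 146, minimum analysable sample 122, f = 0.18, correlation 0.50, two-sided α = 0.025, power 95%, two time points and about 20% dropout all come from the section on power and sample size. The retention threshold and the half-SD example come from the Discussion.

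**1. The plan's own sample size.** For the within-between interaction with two groups and two times, the noncentrality is λ = f² × N × m / (1 − ρ) = 0.0324 × N × 2 / 0.5 = 0.1296 N, with 1 and N − 2 degrees of freedom.
- N = 120 gives 95.2% power, the smallest even N to reach 95%.
- N = 122 gives 95.5%. The stated 122 is reproduced within tolerance.
- 122 × 1.2 = 146.4, which matches the stated 146.

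**2. What each threshold requires.**

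| Rule | Cut-off | Fewest retained | Most lost |
|---|---|---|---|
| Retention above 20% (as written) | 0.20 × 146 = 29.2 | 30 (20.5%) | 116 (79.5%) |
| Retention at least 80% (planned attrition) | 0.80 × 146 = 116.8 | 117 (80.1%) | 29 (19.9%) |

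**3. Can the rule fail?** Treat the number retained as binomial with n = 146 and true retention p; the rule passes with 30 or more.
- p = 0.25: probability of passing 0.91.
- p = 0.30: 0.996.
- p = 0.50: indistinguishable from 1.

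With the cut-off at 117, the probability of passing at p = 0.50 is effectively zero (about 5 × 10⁻¹⁴).

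**4. Information left at the threshold.** To express f = 0.18 in SD units, equate λ with that of a two-sample comparison of change scores. At ρ = 0.5 the SD of change equals the SD of a single score, since √(2(1 − 0.5)) = 1, so λ = N d²/4. Setting N d²/4 = 0.1296 N gives d² = 0.5184 and d = 0.72.

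- 30 completers, d = 0.72: λ = 0.1296 × 30 = 3.89, power 36%.
- 30 completers, d = 0.50: λ = 30 × 0.25 / 4 = 1.875, power 17.6%.
- 117 completers, d = 0.72: power 94.6%.

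These are completer calculations with a near-equal split between arms. They show scale; the planned mixed model would also use partial data.

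**The case against.** Four points can be made for the other side.

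- **The rule is joint.** Retention is required in addition to significance and clinical relevance. With power of 18% to 36% at 30 completers, the efficacy part would more often fail than pass, so the combined rule would not wave through every depleted trial. This stands, and it limits the harm. It does not rescue the retention part, whose purpose is to cover the case where efficacy does pass.
- **It is a visible slip in a Discussion.** It does not touch eligibility, randomisation, outcomes, α, the primary model or participant safety, and a reader can guess the intent from the Attrition section. The limit on scope is right. But this is where the rule is stated, and a rule corrected by guesswork once the data are known is open to the charge of being chosen afterwards.
- **Thirty completers is an extreme.** Earlier trials lost about 10%. That is fair as a forecast, but the written and the evidently intended rule disagree over the whole range from just above 20% to just below 80% retention. At 65% or 75% retention the first passes and the second does not.
- **80% is not exactly what the sample size needs.** The minimum of 122 out of 146 is 83.6%, so 117 retained falls five short. The arithmetic is correct. The cost is small, since 117 still gives 94.6% power, and 80% is the complement of the attrition that the article plans for.

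**Conclusion.** The concern holds. The retention threshold for Phase III contradicts the attrition assumption used in the rest of the article and is wrong as written. It accepts 30 retained and 116 lost out of 146, against about 117 retained and 29 lost under the plan, and it would almost never fail unless true retention fell to about 25% or lower.

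That attrition and retention were interchanged is an inference, though a strong one, because 20% is otherwise used only for loss. The contradiction does not depend on that explanation. The power figures assume a completer analysis, correlation 0.50 and α = 0.025. The error affects the go/no-go decision and not this trial's primary analysis.

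**What to change.** In the Discussion, replace the retention condition with retention of at least 80% (attrition not exceeding 20%), so that it agrees with the Attrition and the power and sample-size sections. In the same sentence, name the visit at which retention is counted. Four months fits the 0- and 4-month basis of the sample size; if the decision is meant to rest on the sustained effect as well, 8 months should be stated instead or in addition. If the authors want the rule to secure the stated minimum of 122, the figure would be 122/146 = 83.6%, and they should say so.

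The cost is one sentence, with no effect on conduct, sample size or analysis. The status section reports 18 participants enrolled by February 2024. The date of the correction should be recorded, to show whether it was made before outcome data were seen.
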